#### Complementary cognitive assessment

During each session, cognition will be assessed using neuropsychological tests (see Table 3). Global cognitive functioning will be assessed with the Montreal Cognitive Assessment (MoCA) [26], and the crystallised intelligence with the Mill Hill part B [27]. Retrospective episodic memory will be assessed with the French adaptation of Grober and Buschke’s procedure [28]. Working memory will be assessed using the Digit Span forward and backward test (Wechsler Adult Intelligence Scale-III [29]), and the binding process will be assessed using a multimodal integration task [30]. During the multimodal integration task, participants have to mentally associate four coloured letters and the location of the cross of the same colour in a grid. Then a grid appears with a black letter, and participants have to indicate if the letter-location corresponds to the letter-location of the mental association. Executive functioning, especially planning, inhibition, shifting, and updating, which are known to be involved in PM functioning, will be assessed respectively with: the Zoo map test [31], the Stroop [32], the Trail Making Test [33], and the N-back task [34].

**Table 3 Tab3:** Neuropsychological tests battery and questionnaires included in the PROSOM-K study, including outcomes measures

Domain assessed	Assessments	Outcome measures	Range
Neuropsychological tests			
Global functioning	MOCA [26]	Total number of correct responses	0–30
	Mill Hill [27]	Total number of correct responses	0–34
Episodic memory	RL/RI-16 [28]	Immediate free recall score	0–48
		Immediate total recall score	0–48
		Delayed free recall score	0–16
		Delayed total recall score	0–16
Working memory	Digit span forward and backward [29]	Total number of correct trials forward	0–16
		Total number of correct trials backward	0–16
	Multimodal integration task [30]	Total number of correct responses	0–20
Executive functions	Zoo map test [31]	Profile score	0–4
	Stroop [32]	interference–colour (time)	≥0 s
	TMT [33]	TMT B–TMT A (time)	≥0 s
		Perseverative errors TMT B (number)	≥0
	N-back [34]	Total number of correct responses	0–48
Questionnaires			
Cognitive self-assessment	Fact-Cog [35]	PCI/PCA/QOL/Oth	0–72/0–28/0–16/0–16
	PRMQ [36]	Prospective score	8–40
		Retrospective score	8–40
Anxiety	STAI [39]	State score	20–80
		Trait score	20–80
Mood	BfS/BfS’ [45]	Total score / Total score	0–56 / 0–56
Depression	BDI [40]	Total score	0–39
Self-esteem	QSR [38]	Valence score	0–100%
		Certainty score	0–100%
Quality of life	FACT-G (patients) [37]	Total score	0–108
Fatigue and somnolence	VAS-F [43]	Energy score / Fatigue score	0–50 / 0–130
	KSS [44]	Total score	1–9
	MFI [41]	General fatigue score	4–20
	FACIT-F (patients) [42]	Total score	0–52
Sleep	Questionnaire of the past 24 h	Sleep efficiency ([total sleep time – total time in bed] x100)	0–100%
	PSQI [47]	Total score	0–21
	ISI [48]	Total score	0–28
	Circadian typology (Horne and Ostberg)	Total score	16–86
Virtual reality discomfort	Simulator sickness [46]	Nausea score	0–27
		Oculomotor score	0–21

*MOCA* Montreal Cognitive Assessment, *RL/RI-16* free recall / cued recall 16 items (French version of the Grober & Buschke procedure), *TMT* Trail Making Test, *FACT-cog* Functional Assessment of Cancer Therapy-Cognitive Function, *PCI* Perceived Cognitive Impairments, *PCA* Perceived Cognitive Abilities, *QOL* impact of PCI on Quality Of Life, *Oth* Others, *PRMQ* Prospective Retrospective Memory Questionnaire, *STAI* State-Trait Anxiety Inventory, *BfS/BfS’* Befindlichkeits-Skala, *BDI* Beck Depression Inventory, *QSR* Questionnaire of Self-Representations, *FACT-G* Functional Assessment of Cancer Therapy-General, *VAS-F* Visual Analog Scale of Fatigue, *KSS* Karolinska Sleepiness Scale, *MFI* Multidimensional Fatigue Inventory, *FACIT-F* Functional Assessment of Chronic Illness Therapy – Fatigue scale, *PSQI* Pittsburgh Sleep Quality Index, *ISI* Insomnia Severity Index

#### Standardised validated self-report questionnaires

During each session, women will complete self-report questionnaires to assess cognitive functioning and psychosocial factors (see Table 3). Cognitive functioning will also be assessed by self-report questionnaires (Functional Assessment of Cancer Therapy Cognitive Scale: FACT-Cog [35] and Prospective Retrospective Memory Questionnaire: PRMQ [36]).

Self-report questionnaires will be used to assess quality of life (Functional Assessment of Cancer Therapy-General: FACT-G [37]), self-esteem (Questionnaire of Self-Representations [38]), anxiety (State-Trait Anxiety Inventory [39]), depression (Beck Depression Inventory [40]), and fatigue (Multidimensional Fatigue Inventory [41], Functional Assessment of Chronic Illness Therapy-Fatigue: FACIT-F [42]). Scale of fatigue (Visual Analogue Scale to Evaluate Fatigue Severity [43]) and somnolence (Karolinska Sleepiness Scale [44]) will be proposed before the learning phase, as well as before and after the phase of intentions retrieval. Mood will be assessed during each session before intentions retrieval by a self-rating mood scale (the Zerssen Befindlichkeits-Skala [45]). Virtual reality discomfort will be assessed by the simulator sickness questionnaire [46] during each session after the virtual reality based task.

#### Sleep assessment

Sleep quality and quantity, circadian typology and insomnia symptoms will be assessed using self-report questionnaires: questionnaire of the past 24 h (routinely used in our research unit, to assess sleep efficiency and sleep quality of the night before the session of familiarisation), Pittsburgh Sleep Quality Index [47], Insomnia Severity Index [48], and circadian typology (Horne and Ostberg) [49]. Every day between the first and the last sessions, participants will fill out a sleep diary to subjectively assess sleep quality and duration, including hours of bedtime, sleep quality, number and duration of nocturnal awakenings and naps.

During all the protocol, participants will wear an actigraph (MotionWatch 8, camNtech) on their non-dominant wrist. Actigraphy will give information related to sleep/activity rhythm, but also related to sleep quality on a longer duration than PSG (around two weeks). The following variables will be extracted: sleep onset latency, total sleep time, sleep efficiency ([actual sleep time – time in bed] x 100), number of nocturnal awakenings after sleep onset. Finally, it will allow to check whether participants took a nap or not during the day-time session or kept awake during the night-time one.

For the night-time session, sleep of participants will be recorded by ambulatory PSG (the gold standard evaluation of sleep quality) at home, in order to assess sleep onset latency, total sleep time, sleep efficiency, relative percentages of sleep stages, sleep efficiency, number of nocturnal awakenings after sleep onset. Twenty electroencephalography (EEG) electrodes will be placed over the scalp, over prefrontal (FP1/FP2), frontal (F3/F4/F7/F8/Fz), central (C3/C4/Cz), temporal (T3/T4), parietal (P3/P4/Pz), and occipital (O1/O2) sites, according to the international 10–20 system; using Ag/Au electrodes with a vertex ground and a bi-mastoids reference. The impedance for all electrodes will be kept below 5 kΩ. The hardware EEG filter band pass will be 0.15–121 Hz and the sample rate will be 256 Hz. Two electrodes will be placed above and under the eyes to record eye movements, as well as two electrodes on the chin to measure muscle tone. An electrocardiogram will also be recorded by placing two electrodes under each clavicle. In order to detect potential sleep apneas or hypopneas, thoracic and abdominal belts will be placed to record respiratory movements, nasal and oral thermistors to measure respiratory airflow and a finger pulse oximeter to measure oxygen saturation. All these sensors will be connected to a Siesta sleep system (Compumedics). Electrodes will be placed by an EEG technician.

### Statistical analysis

This study was designed to control an error risk α of 0.05 and a power of 80%. Assuming cognitive decline for 30% of BC women under HT versus 10% among healthy controls [50], the required sample size is 24 patients per group. We thus planned to enrol a total of 75 participants (25 BC patients receiving HT, 25 BC patients without indication to HT and 25 healthy women).

Descriptive statistics (relative frequency, mean value and SD) will be estimated for the socio-demographic and clinical variables from the total population included in the study. Comparison of means for sub-groups of participants will be realised by Student’s or Wilcoxon’s tests as appropriate. Comparisons of the proportions will be performed using both parametric and non-parametric tests. Link between PM and underlying cognitive functions, HT, and sleep quality, will be estimated thanks to univariate and multivariate logistic regression models, and results will be presented with odds ratios (OR) and their 95% confidence intervals (CI). All analyses will be conducted using R (version 3.4.1).

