## Methods

### Study objectives

The primary objective of the PROSOM-K study is to assess PM performances in BC patients, in order to determine which components (prospective or retrospective), and types of intentions (EB or TB) are the most impaired in BC patients, and specify which cognitive processes (episodic memory, working memory, or executive functions) are particularly involved in PM decline in BC patients.

The secondary objectives are to:clarify the influence of sleep disturbances in BC on PM deficits, using various sleep quality assessments (polysomnography, actigraphy and self-report questionnaires), and by comparing PM scores in two different conditions, depending on the type of delay between encoding and retrieval of intentions: day-time and night-timeassess the influence of HT on PM functioning by comparing PM scores between BC patients treated with HT and BC patients not treated with HT.

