### Participants

The PROSOM-K study will include 25 BC patients treated with radiotherapy alone, 25 BC patients treated with radiotherapy and HT, and 25 healthy women. Patients will be recruited in Centre François Baclesse, a regional cancer centre in Caen (Normandy, France). PROSOM-K protocol will be proposed to eligible patients during a follow-up medical care with their oncologist. Healthy volunteer women, matched for age and years of education with BC patients, will be recruited from our laboratory. Once verified the eligibility criteria (see Table 1) by a physician, each participant will provide her written informed consent to be enrolled in PROSOM-K protocol.

**Table 1 Tab1:** PROSOM-K inclusion and non-inclusion criteria

	Breast cancer patients	Healthy women
Inclusion criteria	1 year post-menopausal	
	Under 70 years of age	
	At least on level 3 (end of primary schools) of the Barbizet scale	
	French native speakers	
	Treated with surgery or radiotherapy for a non-metastatic breast cancer	Normal cognitive function with the Montreal Cognitive Assessment (MOCA) score ≥ 26
	Radiotherapy completed about 6 months prior to the study	–
Non-inclusion criteria	Neurological sequelae	
	Personality disorders and progressive psychiatric disorder	
	Drug use and/or heavy drinking	
	Treated with chemotherapy	History of cancer, excepting basal-cell carcinoma and carcinoma in situ of the uterine cervix
	Patient with a paraneoplastic syndrome	–
	Patient unable to perform cognitive tests	–
	Central nervous system primitive tumour or cerebral metastases	–
	Primitive cancer different from Breast cancer	–
	Metastatic cancer	–
	Cognitive disorders pre-existing to cancer diagnosis	–

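### The 24 per group given for 30% versus 10% is not a two-group sample size; a two-sided comparison at the planned size has about 41–45% power, not 80%

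*Protocol article*

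**What the plan says.** The sample-size paragraph under Statistical analysis opens with "This study was designed to control an error risk α of 0.05 and a power of 80"%. The next sentence gives the effect and the result: "Assuming cognitive decline for 30% of BC women under HT versus 10% among healthy controls [50], the required sample size is 24 patients per group". This is rounded up to 75 participants in three equal groups: "25 BC patients receiving HT, 25 BC patients without indication to HT and 25 healthy women". The paragraph names no test, formula or sidedness, and no allowance for dropout.

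The Participants section confirms that the controls are recruited for this study: "The PROSOM-K study will include 25 BC patients treated with radiotherapy alone, 25 BC patients treated with radiotherapy and HT, and 25 healthy women". The healthy women are matched to the patients on age and education.

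Under Outcome measures, PM retrieval is a total score from 0 to 54. The first part of the stated aim is: "The primary objective of the PROSOM-K study is to assess PM performances in BC patients". A secondary objective compares patients with and without hormonal therapy (HT).

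**The concern.** A difference of 20 percentage points between two proportions is seldom detectable with 24 per group. The figure looked like the answer to a different question: how many patients are needed to show that their rate differs from a known 10%. Here the 10% is to be estimated from 25 healthy women, so its sampling error belongs in the calculation.

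If so, the article credits the study with a power it lacks on its own planning comparison. A non-significant difference in proportions could then be taken as evidence against impairment, on the strength of a claim of adequate power.

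Two related points weaken the justification further. The planning endpoint, a proportion with cognitive decline, is not defined among the outcome measures in the article. The planning contrast, HT patients versus healthy women, is only part of the primary comparison of patients with controls, and it is not the contrast of the HT objective.

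**Working it through.** **Inputs**, all from the Statistical analysis section: α = 0.05, power 80%, p₁ = 0.30 (HT patients), p₂ = 0.10 (healthy women), 24 required and 25 planned per group. Sidedness is not stated. Two-sided is assumed (z = 1.960) and one-sided is shown as a variant (z = 1.645). For 80% power, z = 0.842.

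**1. Reproducing the stated 24.** One-sample test of 30% against a fixed 10%, two-sided:

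n = [(1.960·√(0.1·0.9) + 0.842·√(0.3·0.7)) / 0.20]² = (0.9737 / 0.20)² = 23.7, so **24**.

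This matches exactly. Because the article gives no formula, the one-sample origin is an inference.

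**2. Two independent groups.** The mean rate is (0.30 + 0.10)/2 = 0.20, and the group variances sum to 0.21 + 0.09 = 0.30.

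- Pooled, two-sided: [(1.960·√(2·0.2·0.8) + 0.842·√0.30) / 0.20]² = (1.5697 / 0.20)² = 61.6, so **62 per group**.
- Pooled, one-sided: (1.3914 / 0.20)² = 48.4, so **49 per group**.
- Unpooled, two-sided: (1.960 + 0.842)²·0.30 / 0.04 = 58.9, so 59. One-sided: 46.4, so 47.
- Arcsine, two-sided: 59.01, so 60.
- Continuity-corrected, two-sided: 71.2, so 72.

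None of these comes near 24.

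**3. Power at the planned size**, 30% versus 10%. The pooled normal approximation is Φ[(0.20·√n − 1.960·√0.32) / √0.30]. For n = 25 this is Φ(−0.199) = 42.1%. The chi-square and Fisher figures come from full enumeration of the two binomial distributions.

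| Method | n = 24 | n = 25 |
|---|---|---|
| Pooled normal, two-sided | 40.7% | 42.1% |
| Unpooled normal, two-sided | 43.2% | 44.7% |
| Chi-square, enumerated, two-sided | 43.1% | 45.0% |
| Fisher's exact, two-sided | 31.4% | 30.5% |
| Pooled normal, one-sided | 53.6% | 55.1% |
| Unpooled normal, one-sided | 55.7% | 57.2% |

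For 80% two-sided power with 25 per group and 10% in controls, the HT rate would have to be about 44.5% (44% gives 79.1%).

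**4. Other readings that might rescue 24.**

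- *Both patient groups pooled, 50 versus 25, with 30% assumed in both:* power is 48.6% two-sided and 63.1% one-sided.
- *Matched pairs (McNemar):* n = [(1.960·√ψ + 0.842·√(ψ − 0.04)) / 0.20]², where ψ is the proportion of discordant pairs. The most favourable case possible, ψ = 0.20 with all discordance in one direction, gives 36.8, so 37 pairs. Independence, ψ = 0.3·0.9 + 0.7·0.1 = 0.34, gives 64.3, so 65 pairs.

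**5. What the planned size can do on a continuous score** (two-sided t-test, noncentral t). With 25 versus 25, 80% power is reached at a standardised difference d = 0.81. With 50 versus 25 it is reached at d = 0.70. If 30% versus 10% is read as a shift of a normal score past a common cut-off, then d = z(0.90) − z(0.70) = 0.757. Power is then 75% for 25 versus 25 and 86% for 50 versus 25.

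**The case against.** The strongest objection is that the shortfall belongs to the comparison of proportions, while the main PM measure is a score and the article also plans Student's or Wilcoxon's tests. On the score, the same assumed effect read as a normal shift gives 75% or 86% power, so the shortfall there may be small or absent. This stands, and it limits the consequence: the study is not necessarily underpowered for every planned analysis. It does not rescue the statement, which is made for 30% versus 10% and never argues from the score.

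The 41–45% range also depends on a two-sided test of the chi-square or normal type, which the article does not specify. That is correct. But one-sided power is only about 54–57% and Fisher's exact test gives less, so no reading approaches 80%.

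The related points are fairly contested. HT patients are breast cancer patients, so the planning contrast falls within the primary objective and is a choice rather than a contradiction. The planned logistic regression implies a binary outcome whose cut-off may be defined in the full protocol. These points support rewriting the justification, but the finding does not rest on them.

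Finally, d = 0.70 and d = 0.81 are calculated back from the fixed group sizes and are not expected effects. Pooling the two patient groups presumes similar impairment with and without HT, which a secondary objective sets out to test. Both caveats should accompany any new justification.

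**Conclusion.** The concern holds: the sample-size statement is wrong as written. For 30% versus 10% between two independent groups, α = 0.05 and 80% power require 62 per group two-sided or 49 one-sided, against the stated 24. At 24–25 per group, two-sided power is 41–45%, roughly half of the 80% claimed, and about 31% with Fisher's exact test.

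The conclusion uses only figures printed in the article, plus the fact that the healthy women are an enrolled comparison group. The two-sided test is an assumption, but the one-sided, pooled-patient and matched-pair readings all fall short as well. That 24 came from a one-sample formula is a well-supported inference, and the error stands without it.

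**What to change.** Keep 25 per group and correct the statement. The minimum is to delete the claim that 24 per group gives 80% power, or to replace it with the true figure: about 42% for 30% versus 10% with 25 per group (two-sided 5%, normal approximation). The test and its sidedness should be named.

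Preferably, base the justification on the total PM retrieval score (0–54) with a named primary contrast. With 80% power at two-sided 5%, all patients versus healthy women (50 versus 25) detects d = 0.70, and any pairwise contrast (25 versus 25) detects d = 0.81. These should be presented as detectable differences at a fixed size, and the pooled contrast as assuming similar impairment in the two patient groups. Only one woman per group is spare above the stated 24, and the Discussion provides for withdrawal of women who feel sick after session 1, so the detectable differences should be described as those for complete groups.

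The cost is a rewritten sample-size paragraph with a less favourable power figure. No extra participants or change in procedures are needed. Naming a primary contrast is a design decision for the investigators, but the correction of the power figure does not depend on it.

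### The stated 24 per group does not give 80% power for 30% versus 10%: a two-group comparison needs 62 (49 if one-sided), and 25 per group has about 42%

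*Protocol article*

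**What the plan says.** The sample size rests on three sentences of the protocol article, Statistical analysis. The first sets the error rates: "This study was designed to control an error risk α of 0.05 and a power of 80"%. The second gives the contrast, "Assuming cognitive decline for 30% of BC women under HT versus 10% among healthy controls", and the result, "the required sample size is 24 patients per group". The third draws the consequence, "We thus planned to enrol a total of 75 participants", made up of "25 BC patients receiving HT, 25 BC patients without indication to HT and 25 healthy women".

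Two other statements show which kind of comparison is meant. Under Participants the controls are an enrolled group: "Healthy volunteer women, matched for age and years of education with BC patients, will be recruited from our laboratory". The analysis paragraph adds: "Comparisons of the proportions will be performed using both parametric and non-parametric tests". Neither the sidedness of the test nor the sample-size formula is given, and no test against a fixed reference rate is described.

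**The concern.** Detecting 30% against 10% with 80% power usually takes around 60 per group, so 24 looks too small by a factor of more than two. All the inputs stand next to the result, so the figure can be checked directly.

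The article offers no other reason for enrolling 75 women. If the power is well below 80%, a real threefold rate of decline could easily go undetected. A reader who trusts the stated power would then be inclined to take a non-significant comparison as evidence that decline under HT is no more common than in healthy women.

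This point does not question whether that contrast suits the study's objectives. It asks only whether the number is right for the contrast the article names.

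**Working it through.** **Inputs** (Statistical analysis section): p1 = 0.30, p0 = 0.10, difference 0.20, alpha 0.05, power 0.80, stated n = 24 per group, planned n = 25 per group. Sidedness is not stated, so both cases are shown. Normal quantiles: 1.960 (two-sided), 1.645 (one-sided), 0.8416 (power).

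**1. Reproducing 24.** The one-sample normal formula, with the control rate fixed at 10%, is

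n = [z_α √(p0(1−p0)) + z_β √(p1(1−p1))]² / (p1−p0)²

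- Two-sided: [1.960 × √0.09 + 0.8416 × √0.21]² / 0.04 = (0.5880 + 0.3857)² / 0.04 = 23.7, so 24.
- The one-sided version gives 19.3. A one-sided one-sample arcsine formula gives 23.2, also 24.

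So 24 is matched only by calculations in which a single group is estimated.

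**2. Two independent groups.** With the mean rate 0.20 under the null,

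n per group = [z_α √(2 × 0.20 × 0.80) + z_β √(0.30 × 0.70 + 0.10 × 0.90)]² / 0.20²

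- Two-sided: (1.1087 + 0.4610)² / 0.04 = 61.6, so 62.
- One-sided: (0.9305 + 0.4610)² / 0.04 = 48.4, so 49.

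| Variant | Two-sided | One-sided |
|---|---|---|
| Pooled variance | 62 | 49 |
| Unpooled variance | 59 | 47 |
| Arcsine | 59–60 | 47 |
| Continuity-corrected | 72 | 58 |

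The stated figure is short by a factor of 62/24 = 2.6 two-sided, or 49/24 = 2.0 one-sided.

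**3. Power at 25 versus 25.** Normal approximation, two-sided: (0.20 × √25 − 1.1087) / √0.30 = −0.1985, which gives 42.1%. One-sided: (1 − 0.9305) / √0.30 = 0.127, which gives 55.1%. The exact values sum the probabilities of all pairs of outcomes.

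| Test | Two-sided | One-sided |
|---|---|---|
| Normal approximation, pooled | 42% | 55% |
| Normal approximation, unpooled | 45% | 57% |
| Chi-square without correction, exact power | 45% | 57% |
| Fisher's exact test | 30% | 45% |

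At 24 per group the two-sided figures are 41% (pooled normal), 43% (chi-square, exact) and 31% (Fisher).

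**4. What 25 per group can detect with 80% power (two-sided).** Against a 10% control rate, the patient rate must be about 43% (chi-square, exact), 45% (pooled normal) or 49% (Fisher). For a mean score, the noncentral t distribution gives a standardised difference of 0.81 for 25 versus 25, and 0.70 for all 50 patients versus 25 controls.

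**5. Other readings that might rescue 24.**

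- *Both patient groups pooled, 2:1 against controls:* 49 controls are needed two-sided, 38 one-sided.
- *Matched pairs, in the most favourable form* (20% discordant pairs, all in one direction): [1.960 × √0.20 + 0.8416 × √(0.20 − 0.04)]² / 0.04 = 36.8, so 37 pairs. One-sided it is 28.7, so 29 pairs.

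Neither comes down to 24 or 25.

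**The case against.** Four points can be made for the plan.

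*The article is condensed, and the full protocol may name a formula.* That would excuse an omission. Here a stated result conflicts with the inputs printed beside it, and sidedness, variance formula, pooling and matching have all been tried without reaching 24.

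*The origin of 24 is inferred.* This stands. The article names no formula, and the match depends on an approximation: an exact one-sample binomial test with 24 women has power of only 61% two-sided or 77% one-sided. The finding does not depend on the origin, because 24 is too small for two groups however it was obtained.

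*The 42% looks more precise than it is.* This also stands in part. It is the two-sided pooled normal approximation. The two-sided range is 30% to 45%, and a one-sided chi-square test reaches 57%. A true difference is therefore missed more often than found in every two-sided version, but not with a one-sided chi-square test. No version comes near 80%.

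*The primary objective concerns prospective memory scores, which are continuous.* The 42% indeed says nothing about power for mean scores, and the main score analyses are not shown to be inadequate. The article, however, justifies its size by the proportion contrast alone. It already promises confidence intervals for the odds ratios from its regression models, which limits the risk of misreading a null result but leaves the power statement wrong.

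**Conclusion.** The concern holds. For 30% versus 10% at alpha 0.05, 80% power needs 62 per group two-sided or 49 one-sided, not 24. The planned 25 per group gives about 42% (30% to 45% depending on the test) two-sided and at most 57% one-sided.

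These figures use the article's own rates, two independent groups of equal size and no drop-out. The last assumption favours the plan, since the Discussion foresees withdrawals for virtual-reality sickness and 25 is only one above the stated 24. That 24 came from a one-sample formula is a likely explanation, not an established fact. The correction is necessary because the false 80% is the only stated basis for the sample size.

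**What to change.** Keep the 75 women and rewrite the sample-size paragraph of the Statistical analysis section. Remove the statement that 24 per group is enough. Suggested wording:

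> With 25 women per group, power for 30% versus 10% is about 42% (two-sided, normal approximation; 45% for the chi-square test and 30% for Fisher's exact test by enumeration). For 80% power, 62 per group would be needed. With 25 per group the study has 80% power (two-sided t test, alpha 0.05) for a standardised difference in prospective memory score of 0.81 between two groups, and of 0.70 between all patients and controls.

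The 0.70 applies only if the two patient groups are to be pooled, which the analysis paragraph does not specify; otherwise leave it out. Neither standardised difference needs an assumed standard deviation, but the authors should say whether effects of that size are plausible.

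Add that non-significant comparisons of rates will be reported with confidence intervals and not interpreted as absence of decline.

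The cost is one paragraph and no extra participants. The stated power becomes less favourable.
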